### Data collection tools and technique

Four types of data will be collected in three rounds. These include survey data, and data on cognitive performance, venous blood samples, and daily lentil consumption. Round 1 (baseline) will include all forms of data. Round 2 (midline) at 2 months will only include blood sample data. Round 3 (end of study) at 4 months will include the same data as at baseline (Fig. 2).

**Fig. 2 Fig2:**
[figure not shown]
Flow chart for the 85-day iron-fortified lentil feeding trial. Demographics, food frequency questionnaire (FFQ), anthropometrics, blood test, cognitive assessment

First of all, healthy female adolescents aged 10–17 years, who are non-smoking, not pregnant, and not breastfeeding, and willing to participate will be included in the study. Those who give consent will be invited to attend the BRAC Adolescent Clubs and venous blood samples will be collected in a private setting within the club by a 3-person team consisting of (1) a medical technologist, (2) a female research assistant and (3) a male research assistant. BRAC local staff will be present to monitor the entire process. Albendazole (400 mg in tablet form) will be provided so that participants are dewormed at the time of the feeding trial meaning that they are free from parasites, such as roundworm, flukes, and tapeworm infestation. Earlier studies suggest that worm infestation is linked with anemia and deworming reduces anemia among children [31–33].

All participants will be provided with the contact details of the study coordinator to provide guidance on future questions and concerns. A copy of the consent form will be given to the participants. Publications and scientific presentations of the findings from the study will be presented in aggregate, and the identity of individual participants will be kept confidential. The study will use study codes for hard-copy data documents (e.g., completed questionnaire) instead of recording identifying information and we will maintain a separate document that links the study code to the subjects’ identification information. This document will be locked up in a separate location with restricted access to it (e.g., only allowing access for primary investigators). Laptop computers used by researchers that collect and manage the data will be protected with whole-drive disk encryption that prevents data access if the laptop is lost or stolen. Face sheets containing identifiers (e.g., names and addresses) from survey instruments containing data will be removed after receiving them from study participants. Sensitive identifiers (e.g., names and addresses) will not be permitted to be stored on memory devices or transmitted over unsecured networks. Each researcher will have password-protected, online, cloud-based storage for sharing of study-related files. Study communications will be conducted via secured institutional email servers.

Survey data will include information on socio-demographic characteristics, household food security status, and adolescent food habits obtained using a standardized, food frequency questionnaire (FFQ). Survey data will be collected by the trained enumerators.

Venous blood samples will be collected by a trained phlebotomist; ~ 10 ml of blood will be collected from each participant using lithium heparinized vacutainers following an aseptic procedure and using a disposable syringe and needle. Vacutainers will be transported within 12 h of collection to the International Center for Diarrhoeal Disease Research, Bangladesh (ICDDRB), based in Dhaka. In the state-of-the-art facility laboratory, the serum will be separated and stored at a temperature of 2–8 °C and then analyzed. The blood collection per participant will take about 10 min. We propose to measure complete blood count (CBC), which includes the following: erythrocyte sedimentation rate (ESR), hemoglobin (Hb), hematocrit, packed cell volume (PCV), mean corpuscular hemoglobin (MCH); mean corpuscular volume (MCV) ; mean corpuscular hemoglobin concentration (MCHC), red blood cells (RBC), white blood cells (WBC) total count, differential count, platelet count; sFer, soluble transferrin receptor (sTfR), C-reactive protein (CRP), and blood ABO typing.

Five common measures of attentional (three attention tasks) and mnemonic functioning (two memory tasks) will be used to assess the use of cortical systems and circuits that have been documented to have some dependence on Fe status, based on the literature on either human or animal studies. These measures and tasks have been used extensively in human experiments, and have each been described previously [13, 14]. These computerized assessments will be used to measure attention and visual memory, as used in previous biofortification feeding trials in similar target populations [21–24]. Briefly, all tasks will be undertaken by pre-installed DMDX software (developed by the University of Arizona) and will include detailed instructions and practice tests [25]. This computer-based application will be administered by trained local research assistants.

The simple reaction time (SRT) task provides an estimate of the speed of the simplest possible behavioral response to a visual stimulus and requires a participant to press a button in response to the onset of the task stimulus [26]. The go/no-go (GNG) task provides an estimate of the efficiency of sustained attention and the speed of simple attentional capture without the need to filter information from any immediately competing stimuli [26]. It requires a participant to press a button in response to the presentation of an infrequent stimulus (presented on 20% of the trials) and to withhold a response to a frequent stimulus (presented on 80% of the trials). The attentional network task (ANT) is a modified flanker task that provides an estimate of the effectiveness of three distinct components of attention [27]. In each trial, a participant will be presented with either an informative or an uninformative cue and will be required to press a button to indicate whether an arrow in the center pointed to the left or right while attempting to disregard flanking elements. The cued recognition task (CRT) is a modified version of a classic, visual recognition, memory task that estimates the speed, accuracy, and efficiency of recognition based on short-duration visual memory [28, 29]. Participants will be presented with a set of pictures of common, easily named objects, after which an equal number of previously seen and new items will be presented, and participants will be required to indicate whether each item was in the original set or is new. The Sternberg memory search (SMS) task estimates the speed and accuracy with which immediate visual memory can be searched [30]. In each trial, participants will be first shown a set of 1, 3, or 6 simple graphical symbols to remember, then a test stimulus will be presented, and the participant will indicate whether she remembers the test stimulus from the previous set of symbols. It would take around 45 min per participant.

Data on how much cooked lentil was served to each adolescent girl and how much remained uneaten by each girl will be collected on a daily basis by the research assistants. This information will be used to determine the actual amount of cooked lentil consumed by the adolescents.

### Outcome measurement

#### Assessment of Fe status and anthropometrics

Fe status will be assessed by measuring hemoglobin, hematocrit (volume of red blood cells), sFer, (sTfR), CRP, and imputed total body Fe (TBI). The TBI (mg/kg) will be calculated using the ratio of sTfR to sFer [34].

Participants’ height, weight, waist, hip, and mid-upper arm circumference (MUAC) will be measured to determine change in growth [35–37]. Participants will remain bare-foot, wearing minimal clothing, and we will avoid carpets, sloping, rough, and uneven surfaces when performing anthropometric measurements. The Frankfurt horizontal plane will be ensured when measuring height, and participants will be requested to put their heels together. In addition, their backward curved body parts (buttocks and shoulder blades) and head will be placed against the plane. Participants will be requested to remove shoes and socks and stand still, facing forward, with the palms by their sides, for measurement of weight using a digital body weight bathroom scale. Waist circumference will be measured under the midline of the armpit and at the midline between the inferior part of the last rib and the top tip of the hip bone, using a constant tension tape. Hip circumference will be measured at the point of the maximum diameter of the buttocks using the same constant tension tape, which will also be used to measure the MUAC. First, participants will be requested to put their left arm at 90^°^ angles, and the midline will be marked between the proximal and distal points. The tape will be then wrapped around the point and measured ensuring that the tape will be neither too tight nor too loose. The measurement unit for all anthropometric data will be in centimeters (cm) except for weight, which will be captured in kilograms (kg). Participants’ mean body mass index (BMI) will be calculated using the BMI percentile calculator for children and teens [38].

Dietary intake will be assessed by a field research assistant at baseline and end of study using culturally appropriate FFQs.

#### Cognitive performance

Participants’ attention, and memory (number of correct responses and time (seconds and milliseconds)) will be measured using DMDX software.

### Statistical analysis

Baseline characteristics, i.e., all covariates, will be examined for group comparability to determine if randomization was successful. An intent-to-treat approach will be followed in the analyses of outcome data at the end of the intervention. Outcome variables such as sFer, and Hb will be set using different cutoffs from the National Micronutrients Status Survey 2011–12 [2]. Data will be analyzed with and without adjustment for baseline characteristics. Group means for changes in biochemical variables, anthropometric measures, and post-intervention morbidity rates will be compared using mixed models (with cluster as the random effect), with the respective baseline values serving as the primary covariate. After these preliminary analyses, key outcome variables (sFer and the cognitive performance of the adolescent girls) will be re-examined and additional covariates will be included in the model such as factors that differed by intervention arm, i.e., age, socio-economics, anthropometrics, food security, drinking safe water, hygiene practices etc.). Additional continuous outcome variables will also be examined using a generalized linear model (GLM), adjusted for confounding factors such as age, socio-economics, anthropometrics, food security, drinking safe water, hygiene practices, etc. Categorical variables will be compared using the chi-square test or logistic regression adjusted for possible confounding factors. With the assumption that data will be missing at random (MAR), multiple imputation or likelihood-based mixed models will be used for analysis, after complete case analysis and examination of missing data within and between treatment groups. All outcome variables will be examined for normality, and outliers will be identified. Data collected from adolescent girls suffering from severe Fe deficiency and/or acute infection will participate in all aspects of the study but results of supplementation in this group will be analyzed separately. All analyses will be performed using SPSS for Windows PAWS version 25. A *p* value <0.05 will be considered statistically significant for all main effects.

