### Sample size, randomization and blinding

Considering the lower estimation of the expected difference in mean serum ferritin (sFer) (5 ±20 μg/L) with 80% power at *p* < 0.05 significance level and inter-cluster correlation (ICC) at 0.025, a total of 48 clusters will be selected falling under 16 blocks. Each block will have 3 clubs resulting in a total of 48 clubs. Each club is considered as cluster. Within each cluster, 27 eligible adolescent girls will be selected. Clusters will be randomly assigned to the intervention within each block. In this cluster RCT, units of randomization will be Adolescent Clubs where data will be collected from individual girls. First, a total of 48 clubs will be randomly selected out of 75 clubs. Each cluster will be randomly assigned under 16 blocks. There will be three clusters in each block and three study arms (Fe-fortified lentil, non-Fe-fortified lentil, or usual intake) will be then randomly allocated within blocks using computer-generated random assignments. Equal numbers of clubs (*n* = 16) will be assigned to each arm and there will be equal numbers of participants (*n* = 420) in each arm. Finally, 420 adolescent girls will be included in each arm including an additional 20% to account for loss to follow up. The total sample size including all three arms will be 1260 adolescent girls. For the cognitive testing, a subsample of the intervention group (*n* = 80 adolescent girls in each group, 5 per cluster, a total of *n* = 240 participants) will be selected assuming a two-tailed, 5% type I error rate with 80% power, and an ICC of 0.025. This is based on a recent biofortified iron study with 70% effect size [13, 20]. We further increased the sample size to a total of 360 adolescent girls (e.g., *n* = 120 adolescent girls in each group, considering a 50% attrition rate). We assumed a 20% attrition rate in our first outcome; however, we assume the attrition rate may be higher in the cognitive part as it would take longer, plus many of the participants may have not seen or physically touched a laptop in their lifetime. We assume these will create a greater burden to them resulting in a higher attrition rate. Cluster numbers were sequential at 4-digit point because we wanted to make our UID an 8-digit number: 2 digits for the club ID, 4 digits for cluster, and 2 digits for the participant. This makes the UID more unique and will avoid confusion among the research assistants about each part of the UID. A potential problem with sequential numbering (e.g., 1 .. 16) would be that the different digits used for the participants may lead to different sizes of the UID stickers, and thus to difficulty using the UID stickers during blood sample collection (e.g., on paperwork, blood sample tubes, etc.).

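### Extra covariates for ferritin and cognition are drawn from factors that happened to differ between arms, so the adjusted model follows chance imbalance instead of prognostic value

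*Protocol article*

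**What the plan says.** The Statistical analysis section of the protocol article sets out these steps:

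- Baseline characteristics "will be examined for group comparability to determine if randomization was successful".
- "Data will be analyzed with and without adjustment for baseline characteristics".
- Changes in biochemical and anthropometric measures, and morbidity, are compared using "mixed models (with cluster as the random effect), with the respective baseline values serving as the primary covariate". Ferritin is a biochemical variable and falls under this sentence. Cognition is not mentioned in it.
- The two key outcomes then get a second look: "After these preliminary analyses, key outcome variables (sFer and the cognitive performance of the adolescent girls) will be re-examined".
- On the content of that second model, the section states that "additional covariates will be included in the model such as factors that differed by intervention arm". The factors then named are "age, socio-economics, anthropometrics, food security, drinking safe water, hygiene practices etc".
- "A *p* value <0.05 will be considered statistically significant for all main effects".

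Table 1 gives ferritin and cognitive performance as the primary outcome. The section on sample size, randomization and blinding places 48 clubs in 16 blocks of three and allocates the three arms within each block by computer.

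**The concern.** Under computer allocation within blocks, differences between arms at baseline arise by chance. Examining them cannot show whether randomisation succeeded. A covariate earns its place in the model by predicting the outcome, and an observed difference between arms says nothing about that.

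The rule therefore lets chance decide which covariates enter the adjusted analysis of the two key outcomes. The covariate set is unknown until the data are seen, and the closing etc. leaves it without a boundary. A factor could also qualify because the usual-intake arm differs, which would alter the model for a primary comparison (fortified versus unfortified lentils, Trial objectives) that does not involve that arm.

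The calibration of p values for ferritin and cognition is at stake, together with some precision. The status of the models adds to this. The one model fully described in advance is grouped with the preliminary analyses, and the only modelling sentence that names cognition is the one with the imbalance rule.

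**Working it through.** The article gives no figure of its own on this point, so there is none to reproduce.

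**Inputs from the article:** six named covariate groups (Statistical analysis); 16 clubs per arm, 420 girls per arm and an intracluster correlation of 0.025 for ferritin (sample size section). Girls per club: 420 / 16 = 26.25, taken as 26.

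**Assumptions, not in the article:** a factor counts as differing at p<0.05; the six covariates are independent; each has an intracluster correlation of 0.05; jointly they explain 10%, 30% or 50% of outcome variance.

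**Step 1. How often chance alone triggers the rule.** With k independent covariates, P(at least one differs) = 1 − 0.95^k.

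- k = 6: 1 − 0.735 = 0.265
- k = 10: 1 − 0.599 = 0.401
- k = 15: 1 − 0.463 = 0.537

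The larger k matter because the list is open. Six candidates already allow 2^6 = 64 covariate sets.

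**Step 2. Effect on type I error.** Trials with no treatment effect were simulated: two arms of 16 clubs, 26 girls per club, analysed on club means, 40,000 trials per setting. The Monte Carlo standard error near 5% is √(0.05 × 0.95 / 40,000) = 0.0011, or 0.11 percentage points. Entries are the percentage of trials with p<0.05 for the arm effect.

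| Variance explained | Imbalance judged on | Unadjusted | All six, fixed in advance | Selected by imbalance | Better of unadjusted and selected |
|---|---|---|---|---|---|
| 10% | clubs | 5.01 | 4.91 | 4.69 | 5.38 |
| 10% | girls | 5.14 | 5.30 | 4.58 | 6.10 |
| 30% | clubs | 5.13 | 5.06 | 4.21 | 5.55 |
| 30% | girls | 4.93 | 5.05 | 3.24 | 6.01 |
| 50% | clubs | 4.95 | 5.08 | 3.60 | 5.44 |
| 50% | girls | 4.86 | 5.02 | 2.09 | 5.59 |

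A set fixed in advance keeps the error near 5%. The imbalance-selected model falls below it. Covariates left out of that model are those whose arms happened to be close, so the arm difference varies less than its standard error supposes. Inflation appears only when the more favourable of two results is emphasised.

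The simulation omits the blocks, the third arm and the outcome's own baseline value. Including the baseline value would probably leave less variance for the other covariates to explain, which points to the upper rows of the table.

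**The case against.** Several parts of the other side's case stand.

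- **A model is fixed in advance.** For biochemical outcomes, ferritin included, the article specifies a club random effect and the baseline value. The re-examination can be read as a supporting analysis. A reader might infer that the headline model will be picked from the results. The article does not say so, and naming the headline model may be left to an analysis plan that is not shown. Reporting with and without adjustment is ordinary practice.
- **No test is specified.** Baseline data are to be examined; no test or threshold is given, and the 0.05 level is stated for main effects. The 26% is therefore conditional on an assumed threshold.
- **Age is not ignored.** It comes first in the list, and imbalance is given as an example of what may qualify. The next sentence uses nearly the same list for additional outcomes without any imbalance condition.
- **The p values are not invalidated.** The selected model alone is conservative. Letting the analyst also choose a fully adjusted model raises the error to between 6.9% and 9.0%, but the article does not describe such a third model for the key outcomes.
- **A higher chance of imbalance is not established.** Tests that ignore clubs would flag more covariates. The article does not say clubs will be ignored and gives no intracluster correlation for the covariates; its 0.025 belongs to ferritin.
- **A baseline table has a use.** It can expose problems of conduct, such as selective enrolment. A descriptive table serves that purpose, and adjusting for whatever differs does not repair such a problem.

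None of this removes the stated rule. The words such as, the condition of differing by arm and the closing etc. keep membership of the covariate set dependent on the data, and an analysis plan that follows the article would inherit it.

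**Conclusion.** The point holds as a defect in a stated rule, with modest numerical consequences. Covariates for ferritin and cognition are to be taken from factors that differed by arm, although under the described allocation such differences are chance. The adjusted model is then data-dependent and its p values miscalibrated: 2.1% to 4.7% against a nominal 5% when used alone, and 5.4% to 6.1% if the more favourable of the adjusted and unadjusted results is emphasised. These ranges rest on the simulation's assumptions, chiefly six independent covariates, a 0.05 threshold and an assumed covariate correlation within clubs. With the same threshold and independence, at least one of six covariates would differ by chance about 26% of the time.

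The status of the baseline-adjusted mixed model is unclear for both key outcomes: it is grouped with preliminary analyses, and its sentence does not list cognition.

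**What to change.** 1. Keep the mixed model already described (arm, baseline value of the outcome, club random effect), add the randomisation block, and state that it is the primary model for ferritin and for cognitive performance.
2. Replace the reference to factors that differed by arm, and the open list, with a short set of baseline prognostic covariates named in advance, for example age, socio-economic status and food security. Use it in one supporting model.
3. Delete the aim of judging whether randomisation succeeded, and present baseline characteristics descriptively by arm.

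The cost is wording. The baseline survey already collects socio-demographic and food-security data, cognition is measured at baseline as well as endline, and the article gives the trial status as not yet recruiting. If block enters as a fixed effect, club-level degrees of freedom fall from 48 − 3 = 45 to (16 − 1) × (3 − 1) = 30, a small price for an analysis that follows the allocation. The article appears to place clubs in blocks at random, so the block term may add little precision. The larger gain comes from fixing the covariates in advance.

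### Categorical and additional continuous outcomes are assigned tests with no term for club, although clubs are randomised, so a nominal 5% comparison of two arms is anti-conservative

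*Protocol article*

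**What the plan says.** The section on sample size, randomization and blinding is clear about the unit: "units of randomization will be Adolescent Clubs where data will be collected from individual girls". The sample size allows for this with "inter-cluster correlation (ICC) at 0.025, a total of 48 clusters will be selected falling under 16 blocks".

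The Statistical analysis section then assigns methods in separate sentences.

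- Mean changes in blood measures, anthropometry and morbidity rates are compared with mixed models that have cluster as a random effect and the baseline value as covariate.
- Ferritin and cognition are re-examined with further covariates added to the model.
- "Additional continuous outcome variables will also be examined using a generalized linear model (GLM"), with a list of confounders and no cluster term.
- "Categorical variables will be compared using the chi-square test or logistic regression adjusted for possible confounding factors", again with no cluster term.

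The same section says "Outcome variables such as sFer, and Hb will be set using different cutoffs from the National Micronutrients Status Survey" of 2011–12, which implies categorical versions of both variables. The significance rule is general: a p "value <0.05 will be considered statistically significant for all main effects".

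**The concern.** In a club-randomised trial, girls in one club tend to resemble each other, so the arm difference varies more than independent sampling would suggest. A test that ignores this uses too small a standard error. The article plainly knows this, since it inflates the sample size for it and writes the cluster term into one group of models. The next two method sentences leave the term out, and one of them names a test that in its ordinary form cannot carry it.

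The analyses at stake are those of categorical outcomes and of any continuous outcome outside the mixed-model list. The Discussion explains the value of a 5 μg/L ferritin shift as a fall in iron deficiency from about 30% to about 20%. If that prevalence is compared between arms by the stated method, it will be judged against 0.05 with a test whose real error rate is higher.

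**Working it through.** **Inputs from the protocol article.** Difference 5 μg/L, SD 20 μg/L, 80% power, significance level 0.05 (taken as two-sided; the article says two-tailed only for cognition), ICC 0.025, 16 clubs per arm, 27 girls per club, 420 girls per arm including 20% for loss. After 20% loss, 420 × 0.8 = 336 per arm, and 336/16 = 21 per club. Deficiency prevalence is about 30% (Discussion). Anemia is 17.1% at ages 12–14 (Background).

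**Step 1. Reproduce the article's number of clubs.** Per arm without clustering: n = 2 × (1.96 + 0.84)² × 20²/5², which gives 252. Design effect: DE = 1 + (m − 1) × ICC = 1 + 26 × 0.025 = 1.65. Then 252 × 1.65 = 416 girls, and 416/27 = 15.4, so 16 clubs per arm or 48 in all. This matches and confirms that the ICC enters as a standard design effect.

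**Step 2. Error of a two-arm test that ignores clubs.** Its standard error is too small by a factor √DE, so the true two-sided error is 2 × (1 − Φ(1.96/√DE)).

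If the ICC of the tested outcome is itself 0.025:

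| Girls per club | DE | 1.96/√DE | True error |
|---|---|---|---|
| 21 | 1.50 | 1.600 | 11.0% |
| 27 | 1.65 | 1.526 | 12.7% |

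Beta-binomial simulation (16 clubs per arm, prevalence 5 to 30%, 40,000 runs) gave 10.8 to 11.3% and 12.5 to 12.9%. An overall three-arm chi-square is further off, at 13.6% (21 per club) and 16.3% (27 per club). Clubs are put into blocks at random, so the blocks are not expected to absorb between-club variance.

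**Step 3. If 0.025 is the ICC of a continuous measure that is then cut.** Dichotomising lowers the ICC. Assume a normal underlying variable and, for hemoglobin, borrow the same 0.025. The binary ICC is (p₁₁ − p²)/(p(1 − p)), where p₁₁ is the probability that two girls from one club both fall below the cut.

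| Prevalence | Binary ICC | DE (21 / 27 per club) | True error (21 / 27 per club) |
|---|---|---|---|
| 30% | 0.0144 | 1.29 / 1.38 | 8.4% / 9.5% |
| 17.1% | 0.0115 | 1.23 / 1.30 | 7.7% / 8.6% |

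**Step 4. Range over the ICC of the tested outcome (21 to 27 per club).** ICC 0.01: 7.4 to 8.1%. ICC 0.02: 9.8 to 11.2%. ICC 0.05: 16.6 to 19.6%.

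**Step 5. Does respecting clubs restore the level?** A t-test on club proportions (30 df), used as a stand-in for a clustered logistic method, gave 4.9 to 5.1% in simulation at 20% and 30% prevalence with ICC 0.025.

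**The case against.** Five points can be made for the plan.

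1. **The ICC is borrowed.** The 0.025 is stated for mean ferritin, and nothing is given for a binary outcome or for hemoglobin. A reader might infer that the error is 11 to 13% without condition. The article does not support that: Step 3 gives about 8 to 9% on another reasonable reading. This stands, and the size must be given as conditional. Any positive ICC still inflates the error.
2. **Deficiency and anemia are inferred.** Table 1 lists ferritin and hemoglobin as levels. The cutoff sentence does not name a prevalence endpoint or point to the chi-square sentence, and the fall from 30% to 20% in the Discussion is a rationale, not a planned test. This also stands. The link is the likely reading, because no other sentence gives the categorised variables a method, but it is not stated.
3. **The main outcomes already carry the cluster effect.** This is correct for mean changes in ferritin, hemoglobin and anthropometry. The covariate-adjusted re-examination of ferritin and cognition most naturally uses the same mixed model. The GLM is described as an additional examination, and no outcome is named as falling under it alone.
4. **The chi-square may serve baseline description.** This is possible in part, because the section opens with group comparability. But the sentence comes after the outcome models and offers confounder-adjusted logistic regression, which is an outcome analysis.
5. **Silence is not exclusion, and the article is condensed.** For the logistic model and the GLM, a club term could still be added in a fuller plan. For the ordinary chi-square test it could not. The contrast with the mixed-model sentence makes the omission a stated choice of method and not just a detail left out.

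**Conclusion.** The point holds within limits. As written, the between-arm comparisons of categorical variables and of additional continuous outcomes do not account for club, and their p values will be too small. The true error of a nominal 5% two-arm test is about 11 to 13% if an ICC of 0.025 applies directly to the outcome. It is about 8 to 9% if 0.025 describes an underlying continuous measure cut at 17 to 30% prevalence, and about 7 to 20% over ICCs from 0.01 to 0.05. These figures assume two-sided tests, 16 clubs per arm and 21 to 27 girls analysed per club.

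A reader might go further and conclude that the trial's main result is invalid. The article does not support that, because the mixed-model comparison of ferritin change, on which the sample size rests, includes the cluster random effect. The defect concerns the categorical and additional analyses. It should be corrected before those analyses are run, but it does not threaten the main ferritin comparison.

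**What to change.** Amend the two sentences in the Statistical analysis section.

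- **Categorical outcomes:** state that every between-arm comparison uses mixed-effects logistic regression with club as a random effect, or GEE clustered on club with a small-sample correction, in place of the plain chi-square test or logistic regression. The correction matters with only 16 clubs per arm.
- **Additional continuous outcomes:** state that they use the same linear mixed model, with club as random effect, as the other continuous outcomes.
- **Categorised ferritin and hemoglobin:** say explicitly whether they are tested between arms, so that it is clear which method applies.

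The design, data collection and number of girls do not change. The cost is slightly more analysis work and wider intervals: by a factor of √1.50 = 1.22 to √1.65 = 1.28 if the ICC is 0.025, less if it is smaller. At that ICC, power to detect 30% against 20% deficiency is about 69% (21 per club) to 75% (27 per club). The 85 to 93% that an unclustered calculation shows is not real.
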